### Secondary endpoints

The effectiveness of treatment is examined through MRI and CT follow-ups. Local control rate is defined as freedom from local progression, and local progression-free survival is defined as survival probability from the beginning of radiotherapy until local progression. Disease-free survival is defined as the disease-free time from the beginning of radiotherapy until local or distant progression. The overall survival as a secondary endpoint will be defined as the time from the beginning of radiotherapy until the date of death due to any reason, until the end of the observation period or until the date of the last presentation in case of loss to follow-up (censoring).

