Due to the pilot character of the trial, all analyses are performed descriptively and the results are to be interpreted accordingly. For the primary endpoint, two-sided 95% Agresti–Coull interval is calculated for each treatment group. If missing values occur, multiple imputation based on the “fully conditional specification” method [14] is applied, where treatment group allocation is taken into account in the imputation procedure. Additionally, a complete-case analysis and an analysis according to the ICA-r method are performed [15]. Furthermore, a descriptive comparison of the treatment groups is conducted by application of the chi-square test. Analysis of the secondary time-to-event endpoints LPFS, DFS, and OS is performed by applying the Kaplan–Meier method, where patients without event are censored. The treatment groups are descriptively compared using the logrank test. The secondary endpoint quality of life measured by the EORTC-QLQ30 questionnaire is assessed by presentation of mean, standard deviation, median, minimum, and maximum as well as application of a descriptive two-sample *t* test. For the secondary endpoint local control, absolute and relative frequencies are calculated for each treatment group together with two-sided 95% Agresti–Coull interval and a descriptive chi-square test will be applied for treatment group comparison. Adverse and serious adverse events will be listed, and absolute and relative frequencies will be calculated.

Statistical analysis will be performed by the statistical software SAS v9.4 (SAS Institute, Cary, NC).

The descriptive significance level is throughout 5%, two-sided; all *p* values are to be interpreted as descriptive; and there is no adjustment for multiplicity.

There will be no planned interim analysis. The results of this study will facilitate a subsequent phase III trial.

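### LPFS and DFS do not count death as an event, so deaths without progression are censored and both endpoints read higher than under a death-inclusive definition

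*Protocol article*

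**What the plan says.** The protocol article defines four efficacy endpoints under Secondary endpoints:

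- **LPFS:** "local progression-free survival is defined as survival probability from the beginning of radiotherapy until local progression".
- **DFS:** "Disease-free survival is defined as the disease-free time from the beginning of radiotherapy until local or distant progression".
- **Local control:** "Local control rate is defined as freedom from local progression".
- **OS:** runs "until the date of death due to any reason", with explicit rules for censoring at the end of observation and at loss to follow-up.

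Under Statistical consideration and analysis, LPFS, DFS and OS share one rule. The analysis is "performed by applying the Kaplan–Meier method, where patients without event are censored", and the arms are compared by a descriptive logrank test. Local control is handled differently: "For the secondary endpoint local control, absolute and relative frequencies are calculated for each treatment group", with an Agresti–Coull interval and a chi-square test. A sentence beginning "If missing values occur, multiple imputation based on the" follows the primary endpoint in the same section; it does not mention death.

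**The concern.** An endpoint with survival in its name is normally read as failing at death. Here death is named for OS and for neither LPFS nor DFS, and everyone without the named event is censored. A patient who dies around surgery, from toxicity or from an unrelated cause, with no documented progression, therefore leaves both curves without lowering them. Kaplan–Meier then assumes that the patient's later risk of progression would have matched that of those still followed, which has no meaning after death.

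Two things are at stake. Readers may set these figures beside results from trials that count death. The article also says that the data are to prepare a phase III trial on local control, so the estimates may be used for planning. As written, no endpoint combines local failure with death.

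**Working it through.** **Inputs from the article.** Events and censoring rule as quoted; 32 patients per arm; 12 months of follow-up per patient (Study design), ending 12 months after surgery (Regular study end). No rate of progression, of death without progression or of loss to follow-up is given.

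**The plan's own figure.** The only stated figure is n = 32 per arm, from the Agresti–Coull interval for the primary endpoint. With 0.90 × 32 = 28.8, rounded to 29, and z² = 3.84: ñ = 32 + 3.84 = 35.84; p̃ = (29 + 1.92)/35.84 = 0.863; lower limit = 0.863 − 1.96 × √(0.863 × 0.137/35.84) = 0.750. It reproduces, and neither LPFS nor DFS enters it.

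**One patient traced through the endpoints.** Take a patient who dies in month 3 without progression.

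- LPFS: no local progression, so censored at month 3.
- DFS: no local or distant progression, so censored at month 3.
- OS: event at month 3.
- Local control, read literally: no local progression, so not a failure.
- Primary endpoint: failure if the death is a grade 5 toxicity.

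**Direction.** At each event time j, let r be the number at risk, p the progressions and d the deaths without progression.

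- Death censored: S = Π(1 − p/r).
- Death as event: S = Π(1 − (p + d)/r).

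The risk sets are the same, and each factor in the second product is no larger than in the first. The plan's version can therefore never be the lower one.

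**Size per death, 32 patients, otherwise complete follow-up.**

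- No progression, 1 death: 100% against 31/32 = 96.9%; gap 1/32 = 3.1 points.
- No progression, 2 deaths: 100% against 30/32 = 93.8%; gap 6.3 points, again 3.1 per death.
- 1 death before 4 progressions: 27/31 = 87.1% against 27/32 = 84.4%; gap 2.7 points.
- 1 death after 4 progressions: 28/32 = 87.5% against 27/32 = 84.4%; gap 3.1 points.

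So 3.1 points per death is the ceiling. It is reached when no progression occurs, or none after the death, and it shrinks when progressions follow the death.

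**Range under assumed rates.** Let P be the 12-month risk of progression and D that of death without progression, independent. The gap is (1 − P) − (1 − P)(1 − D) = (1 − P) × D.

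- P = 20%, D = 5%: 80.0% against 76.0%; gap 4.0 points.
- Smallest over P = 10–30% and D = 3–10%: 0.70 × 0.03 = 2.1 points.
- Largest: 0.90 × 0.10 = 9.0 points.

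These rates are assumptions and have no source in the article.

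**Local control.** With 4 progressions and complete follow-up, the crude proportion is 28/32 = 87.5%. The cumulative incidence of progression with death competing is 4/32 = 12.5%, and its complement is the same 87.5%. The two differ only through patients lost early. If one of the 28 is lost before any progression and censored, the incidence is 4/31 = 12.9%, which gives 87.1%.

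**The case against.** The strongest reply is that little depends on this. The endpoints are secondary, descriptive and part of a pilot. Deaths from treatment are not hidden from the trial: a grade 5 toxicity is a failure on the primary endpoint, any death is an OS event, and adverse events are tabulated. One grade 5 toxicity that the monitoring board attributes clearly to the study therapy is a listed reason to end the whole study. The Background also says that patients with this disease die mainly of local recurrence, so deaths without progression within 12 months may be rare. All of this stands, and it limits the consequence. A reader might infer that an arm with excess treatment deaths could pass unnoticed; the documents do not support that.

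It can also be said that the LPFS wording is loose and that the usual meaning was intended. But the article states the event for each endpoint and names death only for OS. This is not a detail left to a fuller document: an analysis plan that added death would depart from the published definitions.

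A reader might extend the point to local control and say that deaths inflate it. That does not hold. Death is defensibly not a local failure, and a competing-risk estimate gives the same figure when follow-up is complete. That patients lost early count as controlled is an inference from the crude proportion, not a statement. The imputation sentence might cover them, although it is written with the primary endpoint. Nor is the missing time point a strong complaint, since the follow-up schedule points to 12 months after surgery.

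Finally, LPFS does not merely repeat local control. It concerns the same event but adds timing and a logrank comparison.

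**Conclusion.** The point holds for LPFS and DFS. As defined and analysed, they are time to local progression and time to any progression, and they are biased upward relative to definitions that include death. The direction follows from the text alone.

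The size does not. It is at most 3.1 points per death without progression among 32 patients, given otherwise complete follow-up, and the number of such deaths is unknown and may be small. A reader might take 3 to 9 points (one to three deaths per arm), or the 2.1 to 9.0 points above, as an expected overstatement. Neither range is supported, because the death counts and rates behind them are assumed.

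The primary endpoint, OS and n = 32 per arm are unaffected. The definitions should be corrected, but the consequence stays within secondary descriptive endpoints.

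**What to change.** Define LPFS as the time from the start of radiotherapy to local progression or death from any cause, whichever comes first. Define DFS as the time from the same origin to local progression, distant progression or death from any cause. Censor only patients alive without the event at last assessment.

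Alternatively, keep the present events, rename the endpoints time to local progression and time to progression, and analyse them with death as a competing event.

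Optionally, report local control as the cumulative incidence of local progression at a fixed time, with death competing and losses censored, so that patients lost early are not counted as controlled.

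The cost is two definitions and, if the option is taken, one analysis line. Dates of death are already needed for OS, so no new data are required. The downside is that LPFS and DFS will look slightly less favourable.

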## Background

Retroperitoneal sarcomas constitute approximately 15% of all soft tissue sarcomas [1, 2]. As the early stages can remain without specific signs or symptoms for a long time, many patients are often diagnosed with large tumors. The main histology is lipo- or leiomyosarcoma and about 60% are high-grade tumors [3]. The primary treatment of patients with retroperitoneal sarcomas is surgery; however, the close proximity to intraabdominal organs hinders resections with wide margins in many cases and about 45% of tumors are resected incompletely (R1/R2) [4]. The risk of local failure is generally high especially when a complete resection cannot be achieved. The general policy for local recurrence is re-operation. Retroperitoneal sarcomas show a lower risk for distant metastases; local control is crucial as the primary cause of death in these patients is local disease recurrence [4–6]. In contrast to extremity sarcomas, most patients die without distant metastases. Preoperative radiotherapy seems to be able to reduce the risk of local recurrence based on data from small sample sized studies and retrospective analyses [1]; at many centers, external beam radiotherapy is combined with an intraoperative radiotherapy [7]. The final publication from the only prospective trial comparing surgery with or without neoadjuvant conventional photon radiotherapy is still awaited. Until now, the role of radiotherapy is substantiated on the role in extremity sarcoma. The toxicity of a preoperative treatment is significantly lower compared to a postoperative treatment; however, the potential for toxicity is significant based on the typically large tumor volumes and precise radiation techniques are required. The special physical and biological properties of protons and carbon ions lead to a superior dose distribution [8, 9]. This allows a better sparing of the surrounding organs at risk, with chances to reduce treatment-related side effects and even potential for dose escalation. Considering the typically large target volumes, reduced dose to the surrounding bowel, kidney, and the hematopoietic tissue in the bone marrow is particularly desirable. Primary phase I data for neoadjuvant proton radiotherapy show promising results with mild toxicity [10]. Additional carbon ions have a higher biological effectiveness and are promising in the treatment of sarcoma and chordoma. The standard neoajuvant normofractionated radiotherapy consists of 25 fractions with 2-Gy single dose over 5 weeks; the special properties of particles allow hypofractionation resulting in a reduced treatment total time of 3 weeks.

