### Treatment planning and target volume delineation

Examinations for treatment planning consist of a CT scan (3-mm slice thickness) in treatment position and a MRI for 3D image correlation. The delineation of the retroperitoneal soft tissue sarcoma requires a T1-weighted post-gadolinium sequence.

Gross tumor volume (GTV) includes the gross tumor based on CT and MRI imaging. The clinical target volume (CTV) is defined as GTV plus surrounding areas at risk for containing microscopic disease. The CTV includes the GTV with a margin of 2 cm. The CTV margins may be smaller if the GTV is adjacent to the critical normal organs like the small bowel. The planning target volume (PTV) includes the CTV with an additional margin of 5 mm in the anterior–posterior direction and 7 mm in the lateral direction to compensate set-up variability. The overlap of PTV and the rectum or intestine is defined as PTV-rectum or PTV-intestine.

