### Toxicity, safety, and quality of life

Toxicity will be evaluated according to International Common Terminology Criteria for Adverse Events (CTCAE) version 5.0 for toxicity (case report forms) and adverse event reporting including the results of clinical examinations as well as imaging studies (MRI or CT). At enrollment, each patient will pass a baseline clinical examination. During treatment, the patient is monitored continuously and acute adverse events will be documented weekly and at the end of treatment. Three weeks after the end of radiotherapy, the patient will receive an MRI, and the surgery is planned 4–6 weeks after RT. The further follow-up presentations are 6 weeks and 3, 6, 9, and 12 months after the tumor resection and include all imaging studies (CT/MRI) (Table 1). The criteria for feasibility and safety are fulfilled, if no grade 3 or higher toxicity has occurred from the start of irradiation until 12 months after surgery, and if the therapy was not canceled due to any reason (unless clearly not treatment related).

**Table 1 Tab1:** Time flow of procedures and examinations

	Study inclusion	Prior to RT	During RT	At the end of RT	3 weeks after RT	OP: 4–6 weeks after RT	6 weeks after RT	3 months after OP	6 months after OP	9 months after OP	12 months after OP
Inclusion and exclusion criteria	x										
Informed consent	x										
Medical history	x		x	x	x		x	x	x	x	x
Evaluation of symptoms and toxicity	x		x	x	x		x	x	x	x	x
Radiotherapy			x								
Resection						x					
MRI abdomen/pelvis		x			x			x	x	x	x
CT thorax		x						x	x	x	x
Quality of life (QLQ-C30)		x			x			x			x

Quality of life (QoL) will be assessed by the means of the EORTC QLQ-C30 questionnaires. Those will be filled out by the patient before treatment, 3 weeks after the end of RT, 6 months after surgery, and at the end of the observation interval of 12 months. The evaluation will be carried out after the complete acquisition of data. Changes in QoL will be determined comparing the results before and after radiotherapy as well as the difference before and after surgery. QoL will be compared between the two arms of the study after the end of radiation and at the end of the observation interval.

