### Statistical consideration and analysis

This study is performed to deliver basic data for the neoadjuvant hypofractionated carbon ion or proton radiation treatment of patients with retroperitoneal soft tissue sarcoma by providing safety and toxicity data for the here presented treatment regimen. The standard treatment is a neoadjuvant normofractionated photon radiotherapy and is considered as the historical cohort which served for the planning of this pilot study including the framework of the safety and feasibility considerations. The randomization will be performed as block randomization at a ratio of 1:1 aiming at equal group sizes by using a web-based randomization tool (randomizer.at).

The primary endpoint is assessed by calculating the two-sided 95% Agresti–Coull interval [13] for each treatment group. The considerations on the choice of the sample size are based on this analysis approach. It is assumed that the proportion of patients treated without grade 3–5 toxicity (CTCAE) up to 12 months after treatment and/or without discontinuation of the treatment for any reason is 0.90. The lower boundary of the two-sided 95% confidence interval should then not fall below 0.75. To achieve this goal under the above assumption, *n* = 32 patients per arm are required.

The intention-to-treat population (ITT) is the primary population for the primary and secondary endpoints and consists of all patients who were included in the study and were treated at least once. The per-protocol population consists of all patients who obtained the allocated treatment as planned and whose documentation is complete. The safety population includes those patients who started treatment (at least 1 day); this is the primary cohort for the analysis of all safety variables.

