### Regular study end

The estimated period of patient accrual is 4 years. The regular end of the treatment period for each patient is 2 to 3 weeks after initiation of radiation therapy (13 fractions, 5–6 fractions per week). The regular end of study participation for each patient is after a follow-up period of 12 months after surgery.

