The randomized phase III STRASS trial is the first randomized trial assessing neoadjuvant RT for 50.4 Gy in 28 fractions for retroperitoneal sarcoma. In total, 266 patients were enrolled and randomly assigned to surgery only or preoperative RT and surgery. In the RT group, 95% of patients received IMRT. In October 2020, the preliminary data with a median follow-up of 43 months were reported in *Lancet Oncology*. The primary endpoint was an increase of the abdominal recurrence-free survival (ARFS) by 20% at 5 years, which was not reached so far. However, in the group of liposarcoma (74.5%), the 3-year ARFS was 71.6% in the surgery and RT group and 60.4% in the surgery group alone [29]. The composite primary endpoint which is not validated consisted of local or distant progression during or after RT, inoperability of tumor or patient defined as ASA score of 3, R2 resection, peritoneal metastases, or local recurrence after resection. There were twice as many local relapses in the surgery only compared to the radiotherapy and surgery group (*N* = 39 vs *N* = 17); thus, the sub-endpoint local recurrence appears clearly in favor of RT. The sub-endpoint progression during radiotherapy assessed on computed tomography 2 weeks after the end of RT was the factor that led to no difference in ARFS. Still, 14 of 16 patients declared as progressed locally received surgery. Furthermore, there were more patients declared inoperable based on the ASA scoring system in the surgery plus radiotherapy group who then received complete resection [30]. Interesting primary endpoints would have been local control alone and survival. There may be some benefit of RT in specific subtypes as liposarcoma and not in others as leiomyosarcoma; however, the trial was not powered to evaluate specific subtypes. Further follow-up might provide additional insight in the future.

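### DFS starts with gross tumour in place and ends only at progression, so R2 and unresected patients count as disease-free until they progress; the quantity is time to progression

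*Protocol article*

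**What the plan says.** All references are to the protocol article.

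- **Definition** (Secondary endpoints): "Disease-free survival is defined as the disease-free time from the beginning of radiotherapy until local or distant progression". No other event is named. Death appears as an event only in the overall survival definition of the same section.
- **Tumour status at the start** (Treatment planning and target volume delineation): "Gross tumor volume (GTV) includes the gross tumor based on CT and MRI imaging". The irradiated target is the tumour itself, still in place.
- **Timing of surgery** (Toxicity, safety, and quality of life): "the surgery is planned 4–6 weeks after RT". Resection comes after the DFS clock has started.
- **Who is analysed** (Statistical consideration and analysis): the ITT population, primary for the secondary endpoints, "consists of all patients who were included in the study and were treated at least once". Patients with R2 resection or no resection stay in.
- **Method** (same section): Kaplan–Meier, "where patients without event are censored", with a descriptive log-rank comparison of the arms.
- **Follow-up** (Regular study end): "The regular end of study participation for each patient is after a follow-up period of 12 months after surgery".
- **Expected resection quality** (Background): "about 45% of tumors are resected incompletely (R1/R2"), R1 and R2 taken together. Entry is open to marginally resectable tumours (Inclusion criteria).

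**The concern.** The definition measures disease-free time from a moment at which no patient is free of disease. Nothing later in the text corrects this: the start is not moved to a tumour-free state after surgery, and a failure to reach that state is not an event.

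Failure to clear the gross tumour is one of the main ways a neoadjuvant strategy can fail, and DFS as written cannot register it. Local control and local progression-free survival do not register it either, because they too fail only at local progression. If one arm had more R2 or unresected patients than the other, the DFS curves and the log-rank test could still look alike. A reader of the results would take the reported DFS to mean freedom from disease, which it is not.

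**Working it through.** **The plan's own figures.** No DFS rate, event number or power is stated, so there is no DFS figure to reproduce. The one design figure, 32 patients per arm, belongs to the primary endpoint. It reproduces with whole patients: 0.90 × 32 = 28.8, rounded to 29, and 29/32 gives an Agresti–Coull lower limit of 0.7500 (0.743 if 28.8 is left unrounded). Nothing below depends on it except the conversion of percentage points into patients.

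**The rule applied to four patients.**

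| Patient | Ever macroscopically tumour-free? | DFS as written |
|---|---|---|
| R0 resection, no recurrence | Yes | No event, censored at end of follow-up |
| R2 resection, residual tumour stable on all scans | No | No event, censored: same as the first patient |
| Never resected, tumour stable | No | No event, censored at last assessment |
| R2 resection, residual tumour grows at the 6-month scan | No | Disease-free until that scan, then an event |

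The second and third patients are scored as the first is. The fourth shows the limit of the problem: a patient who progresses does become an event, only later than the disease status warrants.

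**Size of the bias.** Inputs, none of them given in the documents:
- r: share of patients who are R2 or never resected;
- q: proportion of those who progress by 12 months;
- p: proportion of the remaining patients who progress by 12 months.

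With complete follow-up to 12 months, and leaving death aside:
- DFS as written = (1−r)(1−p) + r(1−q)
- DFS with R2 or non-resection as an event = (1−r)(1−p)
- Difference = r(1−q), which does not depend on p and is never negative.

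Check at r = 10%, q = 50%, p = 15%: 0.90 × 0.85 + 0.10 × 0.50 = 0.815 as written, against 0.90 × 0.85 = 0.765; the difference is 0.05.

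Overstatement in percentage points, with patients per arm of 32 in brackets:

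| r (assumed) | q = 0 | q = 50% | q = 80% | q = 100% |
|---|---|---|---|---|
| 5% | 5.0 (1.6) | 2.5 (0.8) | 1.0 (0.3) | 0 |
| 10% | 10.0 (3.2) | 5.0 (1.6) | 2.0 (0.6) | 0 |
| 20% | 20.0 (6.4) | 10.0 (3.2) | 4.0 (1.3) | 0 |

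**Comparison of arms.** The arms can be distorted unequally. If r were 5% in one arm and 20% in the other, with q = 50% in both, the overstatements would be 2.5 and 10 points, and 10 − 2.5 = 7.5 points of real difference would be missing from the comparison. This is an illustration only; the documents give no reason to expect r to differ between arms.

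**The case against.** **DFS carries little weight in this trial.** It is one of several secondary endpoints, it is not sized, and all p values are declared descriptive. A reader might infer that an inflated DFS would feed into the phase III design. The documents do not support that: the abstract and the Conclusion plan the phase III comparison on local control. This stands, and it limits the consequence to the DFS results themselves.

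**Residual tumour that grows is caught.** MRI is scheduled at 3, 6, 9 and 12 months after surgery. A reader might infer that every R2 or unresected patient counts as disease-free throughout follow-up; that is true only of those who do not progress. For unresected patients the article gives no follow-up anchor, since visits and study end are timed from surgery. How long such a patient is observed is therefore open, and Kaplan–Meier would censor at the last assessment.

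**The size is not known.** A reader might take the 45% in the Background as the share affected. It pools R1 with R2, describes retroperitoneal sarcoma in general and does not cover unresected patients, so it is at most a ceiling for the R2 share of resections. Likewise, r of 5–20% with q of 30–70% would give 0.05 × 0.30 = 1.5 points to 0.20 × 0.70 = 14 points, but that range is assumption throughout and not an estimate.

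**The authors may have left these events out on purpose.** The Discussion describes an earlier trial whose composite endpoint included "inoperability of tumor or patient defined as ASA score of 3, R2 resection, peritoneal metastases, or local recurrence after resection". It calls that composite unvalidated and notes that some patients declared inoperable on ASA score were then completely resected. This is a fair warning about how non-resection is defined. But the criticism is aimed at the ASA-based inoperability and progression-during-radiotherapy components; it does not argue that a patient with macroscopic residual tumour is free of disease.

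**The article is condensed.** The full protocol may say more on unresected patients. The start and the event are nevertheless stated here, and the stated rule is what is at issue, not a missing detail.

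**Conclusion.** The point holds in a limited form. As defined, DFS is time to local or distant progression. R2 and unresected patients count as disease-free until they progress, and for their whole follow-up if they do not. The direction is certain: this rule cannot understate DFS, and it leaves DFS unbiased only if no patient is R2 or unresected or if all of them progress by the time point considered. The size is r(1−q). The documents supply neither term; 5 points at r = 10% and q = 50% is an example resting on two assumptions. The primary endpoint, the sample size and the stated basis for phase III are untouched. What is affected is the DFS curves and their log-rank comparison. The same sentence also omits death, so patients who die without progression would be censored, which is a further upward bias. The correction is worth making because it is cheap and the label as it stands would mislead, not because the trial's main conclusion is at risk.

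**What to change.** Take one of two routes in the Secondary endpoints section.

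1. **Rename.** Keep the definition and call the quantity time to local or distant progression.
2. **Redefine.** Keep the name DFS and count as an event the earliest of: local or distant progression; macroscopically incomplete resection (R2), at the date of surgery; definitive non-resection, at the date of that decision; death from any cause. Define definitive non-resection as never resected within follow-up, so that a patient first judged inoperable but later completely resected is not counted as a failure. This can be settled at the final analysis, as no interim analysis is planned. The present quantity can still be shown beside it under its correct name.

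Either route costs about one sentence. The second also needs resection status and the date of any decision not to operate to be recorded; surgical and pathology reports would be the expected source, though the article does not say so. Under the second route the reported DFS will be somewhat lower.
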